## Abstract

**Background:**

Ovarian cancer is a challenging disease to diagnose and treat effectively with five-year survival rates below 50%. Previous patient experience research in high-income countries highlighted common challenges and opportunities to improve survival and quality of life for women affected by ovarian cancer. However, no comparable data exist for low-and middle-income countries, where 70% of women with the disease live. This study aims to address this evidence gap.

**Methods:**

This is an observational multi-country study set in low- and middle-income countries. We aim to recruit over 2000 women diagnosed with ovarian cancer across multiple hospitals in 24 countries in Asia, Africa and South America. Country sample sizes have been calculated (n = 70–96 participants /country), taking account of varying national five-year disease prevalence rates. Women within five years of their diagnosis, who are in contact with participating hospitals, are invited to take part in the study. A questionnaire has been adapted from a tool previously used in high-income countries. It comprises 57 multiple choice and two open-ended questions designed to collect information on demographics, women’s knowledge of ovarian cancer, route to diagnosis, access to treatments, surgery and genetic testing, support needs, the impact of the disease on women and their families, and their priorities for action. The questionnaire has been designed in English, translated into local languages and tested according to local ethics requirements. Questionnaires will be administered by a trained member of the clinical team.

**Conclusion:**

This study will inform further research, advocacy, and action in low- and middle-income countries based on tailored approaches to the national, regional and global challenges and opportunities. In addition, participating countries can choose to repeat the study to track progress and the protocol can be adapted for other countries and other diseases.

## Introduction

### Global incidence and mortality

Ovarian cancer is the eighth most common cancer and eighth most common cause of cancer death in women worldwide [1]. GLOBOCAN estimates that in 2020 there were approximately 314,000 cases diagnosed, 207,000 deaths, and more than 823,000 women living within five years of their diagnosis. Women in low- and middle-income countries (LMICs) account for 70% of ovarian cancer cases [2]. A 42% increase in ovarian cancer incidence, and a 52% increase in mortality, has been predicted by 2040, with the greatest increase expected in LMICs driven by projected population increases [3, 4]. For example, Zambia is predicted to have an increase of 122% in ovarian cancer incidence and 132% in mortality. Further increases are expected linked to the changing prevalence of cancer risk factors, such as lack of physical activity, changing diets, additional body weight, and increasing urbanisation [5–8].

### Challenges associated with ovarian cancer

Five-year survival for ovarian cancer is below 50% even in high-income countries (HICs), and there has been little progress in improving survival in recent years [9]. Nearly two-thirds of women are diagnosed with advanced disease (FIGO stage III or IV) [10]. A major screening trial using ultrasound and serial measurements of Ca 125 did not demonstrate a mortality benefit and most women are diagnosed after they develop symptoms [11]. Ovarian cancer is a difficult disease to diagnose, and patient and doctor delays are common, in part due to the non-specific nature of the symptoms [12].

At present there is little data from LMICs on the burden of ovarian cancer, including information on types of cancer and stage at diagnosis, pathways to diagnoses, clinical outcomes and the perceptions and experiences of women and their families. Even basic information in incidence is lacking. The proportion of the world’s total population covered by cancer registries included in Cancer Incidence in 5 continents volume XI is just 15%, varying by continent with just 1% of Africa, 7% of Asia and 8% of South America [13]. In addition, many LMICs have prioritised certain cancers in women such as breast and cervical cancer where screening could have a major impact on mortality [14, 15]. The lack of a clear understanding of the burden of ovarian cancer in LMICs and the subsequent lack of focus could hamper the development of approaches aimed at improving ovarian cancer outcomes.

### Known opportunities for progress

Despite these challenges, there are opportunities for short term progress to improve survival, morbidity, and quality of life. Symptom patterns and the nuances of current diagnostic tests are now better understood [16–18], which could contribute to more timely diagnosis. Improved organisation of diagnostic and treatment services and adherence to guidelines show the potential to reduce delays in diagnosis and improve access to treatment, with a likely positive impact on mortality [19–22].

New targeted treatments specifically PARP-inhibitors are emerging for sub-groups of patients. In high-income countries. genetic testing is increasing access to these treatments and improving identification of those most at risk of developing the disease due to their family history [23]. It has been shown that 18% of women with high-grade serous ovarian cancer, the most common and lethal form of the disease, have inherited mutations in BRCA1 or BRCA2 genes [10]. Identifying family members who are at risk, and taking action (e.g. preventative surgery), has the potential to prevent many cases and this approach has already been deemed cost effective in both high- and upper-middle income countries [24]. However, accessibility and affordability of genetic testing and associated targeted treatments for women with ovarian cancer is still very limited in LMICs, thus currently impacting negatively on their outcomes. However this is an opportunity for progress in these settings.

The World Ovarian Cancer Coalition (Coalition) is a partnership organisation of over 200 patient advocacy and support groups from 50 countries with a mission to improve survival and quality of life for women, no matter where they live. In 2018 it undertook The Every Woman Study^TM^, the largest patient experience study to date of women with ovarian cancer. The study included 1531 women from 44 countries, who took part in an in-depth online survey. While the published results showed a common set of challenges, it revealed wide variation between countries on key metrics, highlighting opportunities for improvement [12]. Domains within the study included the route to diagnosis; time to diagnosis; women’s knowledge of the disease pre-diagnosis; family history and genetic testing; access to treatments, surgery and clinical trials; support needs; women’s quality of life; and their priorities for action. However, a key limitation of the study was that 95% of responses came from high-income countries (HICs).

### Aim

In this study, we aim to establish a large patient experience evidence base, and characterise the key challenges and opportunities to improve survival and quality of life for women in LMICs. We will test our hypothesis that key factors vary by country, requiring bespoke potential health strategies. With the evidence obtained from this study we expect to raise the profile of ovarian cancer in LMICs. We hope to enable national teams to engage governments and health policy makers; secure extra funding for diagnostics, research and awareness campaigns; and improve support for women. Examples of this type of approach have been successfully undertaken in high-income countries [25–28].

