### Study infrastructure

To reach sufficient participants and maximise their ability to participate, the OC proposed collaborating with a selection of clinicians treating women with ovarian cancer either known to the Coalition, or through the extensive network of IGCS members. An initial target list of 31 LMICs was drawn up and approaches made to clinicians and national and regional gynecologic oncology societies. In total, 113 clinical sites have been recruited using snowballing methods across 24 countries (Fig 1). Classification of country income level was determined using the World Bank open data, accessed in June 2021 [29].

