**Fig 1 pone.0298154.g001:**
[figure not shown]
Participating countries by income-level World Bank status June 2021.

Within each country, a lead clinician (CLC) was assigned to coordinate the national activity and secure approvals by local or national ethics committees as required. As an example, the protocol submitted in Kenya, is included as a S2 File. CLCs advised on the languages needed and provided contacts for translators who could meet the requirements of the various ethics committees. The survey has been translated into 28 languages using the agencies recommended by the CLCs, and translations checked by back translation where required by national ethics, the clinical team, the study team, and by one or two local patients. The CLC is responsible for the implementation of the protocol, choosing optimal methods of sample selection and data collection for their setting. The CLC is responsible for building their network of participating sites, each with a local site lead (LSL). Depending on the health infrastructure and resources available, countries may have between one and 12 sites, ideally representing the typical range of care women might receive within the country. This is summarised in Fig 2.

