### Data analysis

In our analysis, we seek to examine variation in key metrics (such as stage of ovarian cancer, time to diagnosis and levels of awareness) by country, region and by the socio-economic country group. In addition, we will explore associations between patient and country characteristics and key outcome measures. Table 3 gives some examples of the outcome variables and expected areas for further analysis.

**Table 3 pone.0298154.t003:** Outcome variables and expected further analysis.

Outcome variables		
• Access to chemotherapy • Access to optimal cytoreductive surgery • Access to genetic testing • Level of ovarian cancer knowledge • Time to seek help • Time from seeking help to obtaining a diagnosis • Time from diagnosis to treatment • Information needs •Impact on family finances •Priorities for action		

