**Further analysis**		
**Outcome variables**	**Predictor variables**	**Possible confounders**
Access to chemotherapy	Age on diagnosis Family income Distance to hospital Who pays for ovarian cancer care Resource level of participating site	Stage of ovarian cancer Date of diagnosis Use of neoadjuvant chemotherapy
Access to optimal cytoreductive ovarian cancer	Age on diagnosis Family income Distance to hospital Who pays for ovarian cancer care Resource level of participating site	Date of diagnosis Use of neoadjuvant chemotherapy
Levels of awareness of ovarian cancer	Education level Family income level Distance to hospital Family history	
Time to seek help for symptoms	Age Education level Family income level Who pays for ovarian cancer care First person consulted re symptoms Number of visits prior to diagnosis Level of concern over symptoms Type of symptoms Number of symptoms	

We will perform descriptive and inferential statistics, overall and by country and economic grouping using statistical softwares such as STATA and R. Categorical variables will be summarised with counts and percentages, with Chi Squared Tests or Fisher’s Exact Test used to compare proportions between groups. Continuous variables, such as time to diagnosis, will be examined graphically and summarised using appropriate metrics (mean and standard deviation or median and interquartile range depending on the distribution of the variable data). Tests, such as Kruskal-Wallis, will be applied to continuous variables. Outlying countries will be identified and described.

Appropriate regression analysis approaches will be used to examine assocations between independent and outcome variables. Binary, ordinal or nominal regression will be used depending on the nature of the outcome variable. Univariable regression will be employed to examine individual associations and multivariable regression to examine combined assocations between predictor and outcome variables.

The two free-text answers will be translated, coded and analysed using qualitative content analysis to identify categories and possible themes.

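### The country comparison is to use tests that treat women as independent, although women are clustered in 113 sites; if hospitals differ, the test finds country differences too often

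*Protocol article*

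**What the plan says.** All references are to the protocol article.

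- **Aim** gives the only stated hypothesis: "We will test our hypothesis that key factors vary by country, requiring bespoke potential health strategies".
- **Study infrastructure** describes how women are reached: "113 clinical sites have been recruited using snowballing methods across 24 countries". It adds that "countries may have between one and 12 sites, ideally representing the typical range of care women might receive within the country". The country lead builds the network of sites.
- **Data analysis** examines variation in key metrics "by country, region and by the socio-economic country group". Hospital within country is not among the levels.
- The same section names the methods. Proportions are compared "with Chi Squared Tests or Fisher’s Exact Test used to compare proportions between groups". For continuous measures, "Tests, such as Kruskal-Wallis, will be applied to continuous variables". Outlying countries are then to be identified and described.
- Regression is introduced separately, for associations between predictors and outcomes: "Binary, ordinal or nominal regression will be used depending on the nature of the outcome variable". Table 3 lists the resource level of the site as a predictor for the two treatment-access outcomes only.
- **Sample size** gives country minimums of 70 to 96 women (2,160 in total) for a 95% margin of 10 points, and 1534 women globally for 2.5 points.

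**The concern.** The named tests judge country differences against woman-to-woman sampling error. Women at one hospital share its referral route, staff, resources and administrator. Sites in one country may also use different ways of selecting women (Sample selection). Answers within a hospital will therefore tend to be alike, and a country's result carries the variation of the few hospitals that represent it. The yardstick for whether something varies by country has to include how much hospitals in the same country vary.

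The hypothesis leads to action: country-specific strategies, national reports and engagement with governments. Part of the variation may lie between hospitals. If so, unadjusted tests would credit it to countries, and the response would be aimed at the wrong level.

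**Working it through.** **1. The plan's own figures.** The margin formula is n0 = 1.96² × 0.25 / e², with finite-population correction n = n0 / (1 + (n0 − 1)/N).

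- Country, e = 0.10: n0 = 96.04. For Kenya, N = 2314: 96.04 / (1 + 95.04/2314) = 92.3, stated 92.
- Global, e = 0.025, N = 823,000 (Introduction): n0 = 1536.64, and 1536.64 / (1 + 1535.64/823,000) = 1533.8, stated 1534.
- The country minimums add to 2,160. All but two rows agree with the formula after rounding (Morocco and Vietnam do not), which does not affect this point.

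This formula is for a simple random sample. It contains no allowance for clustering.

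**2. Inputs for the check.** From the article: 24 countries, Table 2 minimums, 113 sites, so 2,160/113 = 19.1 women per site. Assumed: ICC between 0 and 0.10, overall proportion 50%, no true country difference, and the spread of sites over countries.

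**3. Approximate calculation, sites spread evenly.** The design effect is D = 1 + (19.1 − 1) × ICC. The chi-squared statistic on 23 degrees of freedom is inflated by about D, so the 5% critical value of 35.17 acts like 35.17/D.

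| ICC | D | 35.17/D | Chance of rejection |
|---|---|---|---|
| 0.01 | 1.18 | 29.8 | 16% |
| 0.02 | 1.36 | 25.8 | 31% |
| 0.05 | 1.91 | 18.5 | 73% |
| 0.10 | 2.81 | 12.5 | 96% |

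**4. Simulation.** Site proportions were drawn from a beta distribution with the given ICC and no country effect. The test was Pearson chi-squared across 24 countries at 5%. In the even layout every country has 4 or 5 sites. In the uneven layout countries have 1 to 12 sites: six have 1, four have 2, three have 3, two each have 4, 5, 7 and 11, and three have 12, which makes 113.

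| ICC | Even: rejects | Even: countries flagged | Uneven: rejects | Uneven: countries flagged |
|---|---|---|---|---|
| 0 | 4% | 1.1 | 5% | 1.1 |
| 0.01 | 16% | 1.6 | 33% | 2.1 |
| 0.02 | 32% | 2.1 | 64% | 3.2 |
| 0.05 | 74% | 3.6 | 96% | 5.5 |
| 0.10 | 97% | 5.7 | 99.9% | 7.9 |

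Flagged means more than 1.96 standard errors from the pooled value, counted out of 24. A less extreme 1-to-12 layout gave 27%, 55%, 92% and 99.7% rejection at ICC 0.01, 0.02, 0.05 and 0.10.

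**5. Does a site term help?** In the even layout, an F test with site-within-country as the error term rejected 5.5% to 5.8% at ICC 0.01 to 0.10. In the uneven layout, a simple moment estimate of site variance gave 8% to 11%. An F test weighted by site size rejected about 13% to 53% with 1 to 12 sites per country, and an unweighted one about 1% or less. The simple F test is therefore not safe when sites per country are very unequal.

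**The case against.** The strongest reply is that this is a condensed article and detail on clustering may sit in an analysis plan that is not shown. The article promises appropriate regression and gives Kruskal-Wallis only as an example. It also sets no significance level or decision rule for the hypothesis. That rules out saying that site will certainly be ignored. It does not remove the point: the tests named for comparing groups give wrong error rates if followed as written, and regression is described only for predictor-outcome associations.

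Nor is the article blind to sites. Site resource level is a predictor for two outcomes, selection method is recorded per woman with sensitivity analyses planned, and each country's data are reviewed for local bias. Bias from recruiting through known contacts is admitted. None of these allows for correlation within hospitals in the country comparison.

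Three stronger readings are tempting and not supported:

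- **That the reported country differences will be spurious.** The article gives no ICC, and at zero there is no inflation. The Introduction reports wide variation between countries in the 2018 survey, so 24 identical countries is a reference case, not a forecast.
- **That any single-site result describes only that hospital.** For 90 women at one site, 1.96 × √(0.25 × ICC + 0.25 × (1 − ICC)/90) gives 17.2 points at ICC 0.02 and 24.1 at 0.05, against the stated 10. But the Discussion says that in some countries one centre diagnoses and treats the disease. There the hospital is the national service, and this interval does not apply. The article also does not show which countries, if any, have one site.
- **That any test using site as the error term cures the problem.** With very unequal numbers of sites it does not, as the working shows.

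**Conclusion.** The point holds. The tests named for the country comparison assume independence that the recruitment design does not provide. The article gives its own reason to expect hospitals to differ, since sites are meant to span a range of care. With no true country difference, the nominal 5% test rejects in about 15% to 33% of studies at ICC 0.01 and about 73% to 96% at 0.05. Wrongly flagged countries rise from about 1.1 of 24 to between 3.6 and 5.5 at ICC 0.05.

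The direction follows from the design. The size rests on an assumed ICC, an assumed spread of sites, a proportion of 50% and the Table 2 minimums. This should be fixed rather than being fatal to the study, because REDCap data can already be viewed by site (Data management) and the correction can be made at analysis.

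**What to change.** - For the country comparison, replace the unadjusted tests with a mixed model of women within sites within countries: random site effect, country as the factor tested, and a small-sample degrees-of-freedom correction. Do not substitute a simple site-level F test.
- Report between-country and between-site-within-country variation side by side, and identify outlying countries from this model.
- Use the same site term when site resource level is a predictor, because it varies between sites and not between women within a site.
- For a country contributing one site, state that hospital and country cannot be separated from its own data, unless that site is the only centre treating the disease there.

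**Cost.** Analysis wording only, with no new data. The country test loses power, and some apparent country differences will no longer be significant. Control of the error rate may remain imperfect if sites are spread very unevenly: the simple moment correction above still gave 8% to 11%. The mixed model itself was not simulated, so its error rate should be checked on the actual site layout before use.

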## Methods

### Design and setting

The study has been developed by the Coalition, in partnership with the International Gynecologic Cancer Society (IGCS). It is overseen by a global oversight committee (OC) comprising clinical and patient advocates from six geographic areas, together with additional data and diagnostic expertise.

This study adopts a low risk, observational, cross-sectional design. A standardised questionnaire, derived from a previously published set of questions used in an online survey with participants recruited via social media in 2018 [12], has been developed to explore the experiences of women with ovarian cancer in LMICs based on symptoms, route to diagnosis, treatment, and quality of life. This study is designed as a one-off interaction with no follow-up, with recruitment of women via participating hospital clinics to maximise uptake.

### Survey development and modification

The 2018 survey questions were originally developed by analysing structured interviews with eight women who had ovarian cancer. The draft survey underwent repeated testing by 23 women with ovarian cancer from 13 countries, including four middle-income countries [12]. In 2021, a panel of 13 clinicians from eight LMICs were questioned regarding the content validity, cultural sensitivity and importance of the topics and questions used in the 2018 study. Subsequent expert input from the OC, which includes six patient representatives, was obtained. This process reduced the original survey from 148 questions to 59; those considered most relevant and important for the LMIC setting. Almost all questions were multiple-choice, but two questions allowed for free-text input. This reduction in length makes data collection within hospital clinics feasible either on paper, online, or by interview, increasing accessibility for those with limited literacy skills or digital access. Face validity of the survey in English was then tested by eight women with ovarian cancer in hospitals in South Africa, Kazakhstan, Vietnam, and Argentina. All found it an acceptable length, appropriate to their setting and experiences, and not missing any key information. Table 1 shows the question domains, and some sample questions. The OC approved the review process and the final version of the survey (S1 File).

**Table 1 pone.0298154.t001:** Every woman study^TM^ question domains and examples.

Domain	Example questions	
About You 10 questions	Q.6	Just before you were diagnosed, in your view what was your household income? • Below average for your country • Average for your country • Above average for your country • Prefer not to say
Family History 3 questions	Q.11	Have any of the following family relatives (i.e., blood relatives on either your mother or your father’s side of the family) had ovarian cancer? **TICK ALL THAT APPLY** • Mother • Daughter • Sister • Aunt • Cousin • Grandmother (mother’s side) • Grandmother (father’s side) • Other more distant relatives (mother’s side) • Other more distant relatives (father’s side) • No, none of my close family have been affected
Route to diagnosis 14 questions	Q.21	For women who said they experienced symptoms Which type of person, other than a family member, did you **first** seek advice from, about your symptoms? **SELECT ONLY** **ONE** **ANSWER** • A local healer • An alternative health practitioner • A family doctor • A gynaecologist • A gynaecologic oncologist (a doctor specialising in the treatment of ovarian cancer) • A gastroenterologist • An emergency room or accident and emergency doctor • A nurse • A pharmacist • Someone else
Treatments for ovarian cancer 9 questions	Q.29	In deciding what, if any, treatments you will have to control your ovarian cancer or deal with side effects from treatment, which of the following will affect your decision? **TICK ALL THAT APPLY** • The opinion of the doctor • The opinion of my family • I will make up my own mind • The cost of treatment drugs • Other costs associated with treatment such as transport or accommodation • The chance to cure or extend my life • The side effects of treatment • None of the above
Emotional support needs 7 questions	Q.38	For women who have experienced support needs Are there particular issues you have faced? **TICK ALL THAT APPLY** • Fear of the cancer returning • Fear that treatment will not work • Fear of dying • Difficulty with getting back to ‘normal life’ after treatment • Partner or spouse leaving • Other issues relating to family and friends • Feelings of isolation • Feeling unable to talk to others • Loss of fertility • Regaining sexual intimacy with a partner • Coping with the menopause • Dealing with stigma because of the cancer diagnosis • Other • None in particular
Practical support needs 5 questions	Q.47	Has having a diagnosis of ovarian cancer had an impact on your financial situation? **SELECT ONLY** **ONE** **ANSWER** • Yes to a great extent • Yes to some extent • Not much • Not at all • I would prefer not to say
Information needs 5 questions	Q53	If this hospital were able to provide women with information about living with ovarian cancer, what do you think it should include? **TICK ALL THAT APPLY** • Information about treatments and diagnosis • Information about living with ovarian cancer and what to expect • Information on how to manage physical and mental health • Managing ovarian cancer that can no longer be treated • Sources of local or national support • A way to meet other women with ovarian cancer in person or online • The hospital already supplies the information I need • Other • I would not like them to provide information
Final Questions 6 questions including COVID-19, trials, priorities for action	Q.59	Is there something that is particularly important to you about your experience of ovarian cancer that you would like to share with the study team?

